### Ethics and Participant Safety

Project Debunk has received full approval from the Research Ethics Board of The University of Texas MD Anderson Cancer Center in Houston, Texas, and it has undergone a local institutional scientific review. To the best of our knowledge, Project Debunk does not pose any significant risks to the physical and psychological safety of participants. Identities of the participants have been coded and only the research team has access to a master list that links names and study codes. This list is kept in a locked file cabinet. Demographic data and assessments of text messages will be stored on secure servers within the institution. Only aggregate data will be reported. We have obtained a Certificate of Confidentiality from the federal government, which will help to protect the privacy of research participants. The certificate protects against the involuntary release of information about participants collected during the course of covered studies.

## Results

### Status of Results

Data collection is currently underway. Data analysis of change in the main outcomes and writing of the manuscript are expected to be completed in the summer of 2018. We highlight below some of the main baseline findings regarding the study population and measures.

### Sociodemographic Characteristics

Table 1 presents sociodemographic characteristics of the respondents. For the entire sample (n=636), the average age was 20.78 years (SD 2.18), about two-thirds (430/636, 67.6%) were male, and most were black or African American (259/636, 40.7%) or white (236/636, 37.1%). With respect to ethnicity, 36.3% (231/636) of participants were Hispanic or Latino. The study arms did not differ in terms of sociodemographic characteristics or mental health status, economic status, planned education level, numeracy ability, prevention-focus level, receptivity to receiving text messages, or sensation-seeking level (Table 1).

### Tobacco-Related Characteristics

Tobacco-related characteristics of the respondents are presented in Table 2. Of the entire sample, at least once in their lifetime, 45.1% (287/636) have ever used cigarettes, 32.4% (206/636) have ever used cigars, 55.7% (354/636) have ever used hookah, and 26.9% (171/636) have ever used e-cigarettes. In addition, 25.3% (161/636) have ever used marijuana, 47.2% (300/636) have ever used more than one tobacco product, and 43.2% (275/636) have ever used both marijuana and tobacco products.

Among nonusers, 13.4% (47/351) were found to be susceptible to smoking cigarettes, 24.3% (109/449) were susceptible to smoking cigars, 30.4% (86/283) were susceptible to using hookah, and 24.1% (106/440) were susceptible to using e-cigarettes. At baseline, no significant differences between the 8 groups were found with respect to all such tobacco-related characteristics (Table 2).

### Manipulation Checks

We first checked to ensure that the messages were perceived by participants as intended after the first week of message exposure (Table 3). Out of 636 participants, 530 (530/636, 83.3%) completed the manipulation check survey. Compared with gain-framed messages, loss-framed messages were significantly more likely to be perceived as presenting a loss, *F*_7,522_=13.13, *P*<.001. Groups receiving CLE, CLR, SLE, and SLR text messages scored higher on perceived message framing as loss than that of groups receiving CGE, CGR, SGE, or SGR text messages. Complex messages were perceived to be significantly more complex than that of simple messages, *F*_7,520_=2.04, *P*=.05. Groups receiving CLE, CLR, CGE, and CGR messages scored higher on perceived message complexity than that of groups receiving SLE, SLR, SGE, or SGR messages. Emotional messages were perceived to be significantly more emotionally involving than rational messages, *F*_7,520_=6.46, *P*<.001. The groups receiving CLE, SLE, CGE, and SGE messages scored higher on the perceived emotional level of their messages than did the groups receiving CLR, CGR, SLR, or SGR messages (Table 3).

We also checked to make sure that the health messages were consistently perceived as credible (Table 3). As expected, there was no significant difference among the treatment arms with regard to the perceived credibility of message content (*F*_7,520_=1.70, *P*=.10). The total mean score on SMS text message credibility was 7.57 (SD 2.01) on an 8-point scale. This confirms that all text message interventions were perceived to be credible sources of information related to tobacco. Similarly, as shown in Table 3, the treatment arms did not differ with regard to the enjoyment of the messages (*F*_7,520_=0.41, *P*=.90), perceived message relevance (*F*_7,517_=1.04, *P*=.40), or perceived message readability (*F*_7,517_=0.34, *P*=.94).

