### Sample Size Determination

For sample size determination, we conducted a power calculation using the outcome of change in perceived risk of cigarette smoking from baseline to 2 months after each of the campaigns. The 8 study arms define a 2×2×2 analysis of variance (ANOVA) factorial design. Assuming a balanced design in each of the 8 study arms for the change in perceived risk, with n=70 per arm, we have at least 80% power to detect an effect size of 0.12 in a fixed-effects ANOVA. A total of 560 participants are needed to provide 70 participants per study arm at 2 months PC2, with complete measurements at baseline. We assume 11% attrition between the assessment at 7 days after the program and 2 months after the program and 1.5% attrition between baseline and the assessment at 2 months PC2 (ie, a total of 12.5% attrition). As a result, our retention rate is expected to be 87.5%. This assumes 640 participants randomized to 8 study arms. This sample size was calculated using PASS 2005 (NCSS, LP).

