### Current Data Analysis

For the currently available baseline data, we used descriptive statistics to summarize sociodemographic characteristics (eg, age, gender, and race), tobacco-related characteristics (tobacco use and number of friends who use tobacco), and primary psychosocial health outcomes (ie, perceived risk of using each tobacco product).

Using the currently available data from the first weekly manipulation check survey, we checked to make sure that the message structures were perceived by participants as intended. Using one-way ANOVA, we examined study arm differences in perceived message loss framing, complexity level, emotional level, credibility, message enjoyment, perceived message relevance, and perceived message readability. STATA version 14 statistical software was used for data analysis.

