### Planned Data Analysis

Once the trial is complete, we plan to conduct an exploratory analysis to identify which combination of message characteristics (ie, depth, framing, and appeal) most increases perceived risk of using each type of tobacco product. This analysis is exploratory because to date no theoretical framework or empirical evidence has been presented that demonstrates the importance of one message structure over another in the context of tobacco risk communication. We will first conduct, a series of 8 repeated-measures mixed-effects models for each type of tobacco product with the interaction effect (group [one combination vs all other combinations] × time [baseline, 2 months PC1, and 2 months PC2]) to predict perceived risk of using the product. These models will control for past 30-day use of the product at baseline and the crossover group assignment. In addition to the main outcomes analyses, we plan to conduct several moderation analyses, including the examination of different groups such as gender, race, mental health status, and personality types. This analysis will allow us to check if different types of individuals may respond differently to certain structures of text messages. Repeated-measures mixed-effect models with interaction effects will be conducted. For all data analysis, *P*<.05 is considered statistically significant. We will use STATA version 14 software (StataCorp LLC) for all analyses.

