**Susceptibility to use^l^**										
	Cigarettes	46 (13.2)	7 (15.9)	2 (4.7)	2 (4.4)	9 (19.6)	7 (18.3)	6 (15.8)	4 (9.5)	9 (18.8)
	Cigars	96 (22.7)	14 (24.1)	4 (7.8)	7 (14.9)	19 (29.2)	18 (26.1)	10 (16.7)	10 (18.2)	14 (23.7)
	Smokeless	80 (13.3)	14 (17.7)	5 (6.6)	7 (10.5)	13 (16.7)	10 (11.9)	8 (11.4)	10 (14.1)	13 (16.7)
	Hookah	85 (30.1)	19 (48.7)	6 (17.7)	12 (30.8)	10 (28.6)	11 (32.4)	8 (24.2)	6 (18.2)	13 (37.1)
	e-Cigarettes	125 (26.9)	21 (35.59)	13 (22.4)	11 (20.4)	16 (26.7)	13 (21.7)	18 (31.6)	14 (24.6)	19 (31.7)
Use marijuana and tobacco		275 (43.2)	40 (49.4)	39 (50.6)	26 (35.6)	34 (42)	38 (43.7)	32 (40.5)	31 (40.3)	35 (42.7)
Secondhand smoke in house		68 (10.7)	10 (12.3)	9 (11.7)	10 (13.7)	7 (8.6)	6 (6.9)	4 (5.1)	12 (15.6)	10 (12.2)
Have friends who use tobacco		566 (89.0)	76 (93.8)	67 (87.0)	60 (82.2)	68 (84.0)	80 (92.0)	69 (87.3)	72 (93.5)	74 (90.2)

^a^Results that include *Ever* product use followed by *Past 30 days* use (p30).

^b^Randomization of participants to 8 groups of short message service text messages.

^c^CGE: complex, gain-framed, emotional.

^d^CGR: complex, gain-framed, rational.

^e^CLE: complex, loss-framed, emotional.

^f^CLR: complex, loss-framed, rational.

^g^SGE: simple, gain-framed, emotional.

^h^SGR: simple, gain-framed, rational.

^i^SLE: simple, loss-framed, emotional.

^j^SLR: simple, loss-framed, rational.

^k^Refers to the concurrent use of multiple tobacco products among participants at any time.

^l^Susceptibility to use is measured with nonusers only.

**Table 3 table3:** Week 1 manipulation check outcomes for the total sample and by treatment arm.

Outcomes^a,b^	Mean (SD)									*P* value^k^
	Total	CGE^c^	CGR^d^	CLE^e^	CLR^f^	SGE^g^	SGR^h^	SLE^i^	SLR^j^	
Perceived message-framing as a loss (8-point scale)	5.20 (3.22)	3.74 (2.23)	4.39 (3.00)	5.74 (3.25)	7.58 (2.86)	4.07 (2.66)	4.17 (3.04)	6.06 (3.33)	6.00 (3.41)	<.001
Perceived complexity level (8-point scale)	2.98 (2.02)	3.07 (2.12)	2.81 (2.26)	3.34 (2.33)	3.60 (2.14)	2.45 (1.54)	2.86 (1.95)	3.05 (1.96)	2.78 (1.81)	.05
Perceived emotional level (8-point scale)	3.35 (2.23)	3.72 (2.13)	2.24 (1.52)	4.39 (2.72)	3.39 (2.33)	3.62 (2.22)	2.80 (1.90)	3.82 (2.28)	2.86 (1.97)	<.001
Perceived credibility (8-point scale)	7.57 (2.01)	7.43 (1.85)	8.01 (1.78)	7.60 (1.90)	7.87 (1.80)	6.98 (2.45)	7.70 (1.96)	7.36 (2.01)	7.64 (2.09)	.10

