## Discussion

### Overview

The Project Debunk trial will evaluate a comprehensive campaign delivered by mobile phone for increasing tobacco risk perception among a large sample of young adults in community college, including both tobacco users and nonusers. In particular, the trial will identify which structures of SMS text messages, if any, have the strongest effect on increasing the perceived risk of using conventional tobacco products and NETP. The results of this study will form the basis of an evidence-based resource that future researchers and practitioners could modify for use among their populations of interest.

To the best of our knowledge, this is the first published mHealth protocol for a trial that assesses the effect of a comprehensive and evidence-based mobile phone text messaging campaign for tobacco risk communication. This protocol summarizes the design and describes the planned evaluation of Project Debunk. Going beyond a simple presentation of our future study procedures, the protocol also presents the results from our baseline data. In particular, baseline information confirms that a substantial proportion of young adults at community colleges continue to smoke cigarettes, in addition to using NETP such as e-cigarettes and hookah. There were no differences among the treatment arms with respect to sociodemographic or tobacco-related characteristics. In addition, the treatment arms did not differ at the baseline with respect to the perceived risk of using any tobacco product. Preliminary results also show that we have successfully manipulated the 8-message structure combinations with our study sample. This is evident from treatment arm differences with respect to perceived message loss framing, emotional level, and complexity. All 8-message structure combinations were found to be enjoyable, easy to read, and credible.

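### The week-1 manipulation check reports 8-arm omnibus F tests as tests of framing, depth and appeal, and its arm-by-arm statement on complexity conflicts with Table 3

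*Protocol article*

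**What the plan says.** Under Sample Size Determination the article states that "The 8 study arms define a 2×2×2 analysis of variance (ANOVA) factorial design". The check on message perception does not use that structure. Current Data Analysis says: "Using one-way ANOVA, we examined study arm differences in perceived message loss framing, complexity level, emotional level, credibility", followed by enjoyment, relevance and readability.

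Manipulation Checks then words the results as two-level comparisons. For depth it reports: "Complex messages were perceived to be significantly more complex than that of simple messages, *F*_7,520_=2.04, *P*=.05". The framing claim carries F(7,522)=13.13 and the appeal claim F(7,520)=6.46. Each claim is followed by a list of arms said to score higher than the rest. The list for depth reads: "Groups receiving CLE, CLR, CGE, and CGR messages scored higher on perceived message complexity than that of groups receiving SLE, SLR, SGE, or SGR messages".

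For credibility, on F(7,520)=1.70 and P=.10, the section says that "there was no significant difference among the treatment arms with regard to the perceived credibility of message content". The Discussion (Overview) concludes: "Preliminary results also show that we have successfully manipulated the 8-message structure combinations with our study sample". Planned Data Analysis sets the significance rule: "For all data analysis, *P*<.05 is considered statistically significant".

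**The concern.** An F test with 7 numerator degrees of freedom asks whether any of the eight arm means differ. A significant result does not say that depth, framing or appeal is responsible, and a non-significant one can hide a difference along a single factor. The design offers a direct test of each factor, and it was not used.

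The sentence on complexity can also be checked against the article's own table. The parallel sentences for framing and emotional level are true arm by arm, so a reader will take this one the same way, and it is not.

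The trial exists to link changes in perceived risk to message structure. Readers will use this check to judge how well each structure was delivered and what else varied with it. Weekly checks continue through both campaigns, so the same analysis could be repeated.

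**Working it through.** **Inputs.** Arm means and SDs are from Table 3. The reported denominator df imply 530 respondents for framing and 528 for the other three scales. Respondents per arm are not given. I assume equal arms (66.25 or 66 each) and, as a check, respondents proportional to the randomized arm sizes 81, 77, 73, 81, 86, 79, 77, 82 implied by Table 1.

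**Step 1: arm ordering on complexity.** From low to high: SGE 2.45, SLR 2.78, **CGR 2.81**, SGR 2.86, SLE 3.05, CGE 3.07, CLE 3.34, CLR 3.60. The sentence fails for CGR against SGR and against SLE. In pairs that differ only in depth, complex minus simple is CGE−SGE +0.62, CGR−SGR −0.05, CLE−SLE +0.29, CLR−SLR +0.82.

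**Step 2: reproduce the reported F values.** With equal arms, MSE is the mean of the squared SDs, the between-arm mean square is n·Σ(mean − grand mean)²/7, and F is their ratio.

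| Scale | Between-arm mean square | MSE | F, equal | F, proportional | Reported |
|---|---|---|---|---|---|
| Loss framing | 66.25×12.458/7 = 117.9 | 8.969 | 13.15 | 13.43 | 13.13 |
| Complexity | 66×0.8894/7 = 8.386 | 4.113 | 2.04 | 2.11 | 2.04 |
| Emotional level | 66×3.2884/7 = 31.00 | 4.662 | 6.65 | 6.44 | 6.46 |
| Credibility | 66×0.7180/7 = 6.770 | 3.962 | 1.71 | 1.75 | 1.70 |

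The reported values are therefore omnibus 8-arm tests. F(7,520)=2.04 corresponds to p=0.0485.

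**Step 3: 1-df factor contrasts.** Each is the mean of four arms minus the mean of the other four. SE = √(MSE·Σ(1/nᵢ)/16), which with 66 per arm is √(MSE/132). The standardized effect is d = difference/√MSE. For depth on complexity: 3.205 − 2.785 = 0.42; SE = √(4.113/132) = 0.1765; F = (0.42/0.1765)² = 5.66; d = 0.42/2.028 = 0.21.

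| Contrast (equal arms) | Difference (95% CI) | F, 1 df | p | d |
|---|---|---|---|---|
| *Intended:* framing on loss | +2.25 (1.74 to 2.76) | 75.0 | <.001 | 0.75 |
| *Intended:* appeal on emotional level | +1.07 (0.70 to 1.43) | 32.1 | <.001 | 0.49 |
| *Intended:* depth on complexity | +0.42 (0.07 to 0.77) | 5.66 | 0.018 | 0.21 |
| *Unintended:* framing on complexity | +0.395 (0.05 to 0.74) | 5.01 | 0.026 | 0.19 |
| *Unintended:* framing on emotional level | +0.52 (0.15 to 0.89) | 7.66 | 0.006 | 0.24 |
| *Unintended:* appeal on loss (emotional lower) | −0.63 (−1.14 to −0.12) | 5.91 | 0.015 | −0.21 |
| *Unintended:* appeal on credibility (emotional 7.34, rational 7.81) | −0.46 (−0.80 to −0.12) | 7.13 | 0.008 | −0.23 |

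Proportional arms change these p-values by less than 0.001. Over 3000 random splits of respondents across arms, p ranged over 0.017–0.018 for depth on complexity, 0.025–0.026 for framing on complexity and 0.0076–0.0088 for appeal on credibility.

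**Step 4: how the omnibus test hides a factor effect.** With equal arms the 7-df F is the average of the seven 1-df F values (three factors, four interactions). For credibility: (7.13 + 3.15 + 0.26 + 0.18 + 0.05 + 1.17 + 0.04)/7 = 11.98/7 = 1.71, so an appeal F of 7.13 is diluted to P=.10. For complexity the seven sum to 7×2.04 = 14.28. Depth supplies 5.66/14.28 = 40% of the between-arm variation and framing 5.01/14.28 = 35%.

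**Step 5: multiplicity and scale.** Seven scales by three factors give 21 contrasts, so a Bonferroni threshold is 0.05/21 = 0.0024. None of the unintended effects meets it. The credibility row also shows a CGR mean of 8.01 (SD 1.78) on a scale labelled as 8-point, which is impossible if the maximum is 8.

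**The case against.** The strongest reply is that the article's directional conclusions are right. All three intended contrasts are positive and nominally significant on 1 df, and complex arms do score higher on average. The CGR shortfall against SGR is 0.05, with a standard error of about 0.35. Messages were also validated before the trial by expert and student agreement of at least 70% and by word counting. The planned outcome models compare one combination with all others, so the check does not enter them. On credibility, the text reports no significant difference and concludes that messages were credible; it does not claim equivalence by appeal. All of this stands, and it limits the point to analysis and reporting.

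Two stronger readings are tempting, and the documents support neither.

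- A reader might infer that, because framing also moves perceived complexity, a later depth result could not be read as a complexity effect. But framing is crossed with depth by randomization. Each depth level contains both framings, so the framing effect cancels from the depth contrast. The depth×framing interaction on complexity is 0.135 (p=0.44). What the overlap bears on is the reading of a framing result.
- A reader might infer that credibility confounds the appeal comparison. It was measured after randomization and after a week of messages. If appeal changes it, it is a consequence of appeal and possibly a mediator, not a confounder.

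What the reply does not rescue is the sentence that contradicts Table 3, or the use of 7-df F values as evidence for two-level claims.

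**Conclusion.** The point holds as a correction that should be made to the analysis and reporting of the check; it is not a flaw in randomization, outcome or sample size. The complexity sentence is wrong for one of the four complex arms, which needs no assumption to see. The reported F values do not test the factor claims they accompany. A proper test supports those claims with unequal strength: framing d=0.75, appeal d=0.49, depth d=0.21. Depth is the weakest manipulation, and framing shifts the same scale by a similar amount (d=0.19).

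The unintended effects, including lower credibility of emotional messages (−0.46), are small, post hoc and above the Bonferroni threshold. They are signals to report, not established facts, and the credibility one depends on resolving the scale. The contrasts rest on rounded Table 3 values and an assumed split of respondents across arms, to which they are insensitive.

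**What to change.** 1. Analyse each perception, in this check and in the later weekly ones, with a 2×2×2 factorial ANOVA. Report the 1-df effect of the intended factor and of the two unintended factors, with confidence intervals; the omnibus F can stay beside them.
2. Correct the complexity sentence to say that complex arms scored higher on average (about 3.2 versus 2.8), with CGR an exception.
3. Check the scoring and range of the credibility scale, and correct either the label or the values in Table 3.
4. Qualify Manipulation Checks and the Discussion overview: depth was weakly manipulated, and credibility showed a possible difference by appeal, to be treated as a possible mediator when appeal effects are interpreted.

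The cost is a re-run of Table 3 on data already collected and some rewording. Nothing in the conduct of the trial changes.

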### Baseline Treatment Arm Differences in Outcome Measures

At baseline, there were no significant differences among the treatment arms with respect to our risk communication variables: perceived risk of using each tobacco product, perceived personal and general benefits of e-cigarettes, perceived addictiveness of products, or perceived popularity of tobacco use (Table 4).

**Table 1 table1:** Baseline sociodemographic characteristics for the total sample and by treatment arm.

Characteristics		Statistics^a,b,c^								
		Total	CGE^d^	CGR^e^	CLE^f^	CLR^g^	SGE^h^	SGR^i^	SLE^j^	SLR^k^
Gender at birth (men), n (%)		430 (67.6)	53 (65.4)	52 (67.5)	54 (74.0)	60 (74.1)	56 (65.1)	56 (70.9)	44 (57.1)	55 (67.1)
**Race, n (%)**										
	Hispanic or Latino ethnicity	231 (36.3)	31 (38.3)	29 (37.7)	24 (32.9)	28 (34.6)	30 (34.9)	34 (43.0)	22 (28.6)	33 (40.2)
	Asian	99 (15.6)	12 (14.8)	15 (19.5)	13 (17.8)	9 (11.1)	14 (16.3)	7 (8.9)	16 (20.8)	13 (15.9)
	Black or African American	259 (40.7)	34 (42.0)	28 (36.4)	33 (45.2)	39 (48.1)	33 (38.4)	30 (38.0)	31 (40.3)	31 (37.8)
	White	236 (37.1)	31 (38.3)	29 (37.7)	21 (28.8)	29 (35.8)	36 (41.9)	31 (39.2)	24 (31.2)	35 (42.7)
	Other	42 (6.6)	4 (4.9)	5 (6.5)	6 (8.2)	4 (4.9)	3 (3.5)	11 (13.9)	6 (7.8)	3 (3.7)
Have children, n (%)		58 (9.1)	7 (8.6)	8 (10.4)	8 (11.0)	5 (6.2)	5 (5.8)	9 (11.4)	9 (11.7)	7 (8.5)
Age (years), mean (SD)		20.92 (2.52)	20.53 (2.21)	21.03 (2.10)	20.75 (2.10)	20.89 (2.30)	20.55 (2.06)	20.97 (2.25)	20.86 (2.22)	20.66 (2.22)
Mental health status, mean (SD)		67.33 (19.18)	67.80 (18.01)	64.83 (18.80)	68.11 (19.16)	69.43 (19.32)	67.53 (18.74)	68.30 (19.02)	67.17 (20.42)	65.46 (20.33)
Economic status, mean (SD)		2.77 (0.92)	2.67 (0.96)	2.79 (0.96)	2.74 (0.96)	2.68 (0.93)	2.84 (0.89)	2.96 (0.81)	2.77 (0.97)	2.71 (0.90)
Planned education level, mean (SD)		3.67 (1.15)	3.77 (1.10)	3.75 (1.05)	3.53 (1.28)	3.81 (1.16)	3.66 (1.06)	3.72 (1.09)	3.52 (1.25)	3.61 (1.24)
Numeracy ability, mean (SD)		5.35 (1.81)	5.41 (1.61)	5.51 (1.82)	5.29 (2.00)	5.15 (2.04)	5.56 (1.69)	5.20 (1.86)	5.39 (1.73)	5.27 (1.74)
Prevention-focus level, mean (SD)		2.81 (0.69)	2.73 (0.71)	2.90 (0.73)	2.86 (0.67)	2.77 (0.72)	2.80 (0.70)	2.80 (0.64)	2.79 (0.72)	2.82 (0.68)
Receptivity to receiving text messages, mean (SD)		0.92 (0.15)	0.94 (0.12)	0.90 (0.22)	0.90 (0.15)	0.89 (0.18)	0.92 (0.13)	0.95 (0.11)	0.94 (0.10)	0.93 (0.14)
Sensation-seeking level, mean (SD)		3.50 (0.83)	3.50 (0.73)	3.47 (0.85)	3.34 (0.91)	3.45 (0.86)	3.56 (0.78)	3.60 (0.84)	3.51 (0.85)	3.55 (0.81)

^a^Missing values are not presented in this table.

^b^Participants were randomized to one of the 8 treatment arms, describing the type of messages.

^c^Proportions in subsample and percentage are presented for categorical variables, and the mean with SD are presented for continuous variables.

^d^CGE: complex, gain-framed, emotional.

^e^CGR: complex, gain-framed, rational.

^f^CLE: complex, loss-framed, emotional.

^g^CLR: complex, loss-framed, rational.

^h^SGE: simple, gain-framed, emotional.

^i^SGR: simple, gain-framed, rational.

^j^SLE: simple, loss-framed, emotional.

^k^SLR: simple, loss-framed, rational.

**Table 2 table2:** Tobacco-related characteristics for the total sample and by the group at baseline.

Substance use^a^		N^b^ (%)								
		Total	CGE^c^	CGR^d^	CLE^e^	CLR^f^	SGE^g^	SGR^h^	SLE^i^	SLR^j^
